#### Statistical analysis

Over the course of the intervention, we will utilize a repeated-measure, mixed-model approach in order to identify significant changes in the main outcome variables between the three groups. Differences in baseline PTSD symptom severity will be considered to acknowledge nonlinear treatment effects between participants with a different burden at t_1_. Potential confounding variables, such as the exposure to potentially traumatic events during the course of the intervention, will be used as covariates. All analyses will be performed using R statistics and MPlus.

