## Methods/design

### Participants

This study investigates juvenile trauma victims from the Democratic Republic of the Congo (DRC), aged 13–16 years, who are based at the Nakivale refugee settlement, an official refugee camp in Uganda, Africa, which is among the largest refugee camps in the world. The government of Uganda and its United Nations High Commissioner for Refugees (UNHCR) partners provide general health services to the refugees in the settlement with few psychotherapeutic interventions. Therefore, Ainamani, Elbert, Olema, and Hecker [46] propose the ample provision of trauma-focused treatment options particularly in these settings in order to support not only individual traumatized refugees but also their families and the whole community. All participants will have a history of traumatic experiences. Participants eligible for inclusion in the intervention only involve individuals with a diagnosis of PTSD according to the *Diagnostic and Statistical Manual of Mental Disorders* (DSM-V). Exclusion criteria cover (1) acute suicidality, acute intoxication, or psychotic symptoms, (2) inability of the parent or legal guardian to provide consent, or (3) child protection issues (e.g., acute maltreatment) that are identified during the initial cross-sectional assessment and are judged by a clinician to make trial inclusion inappropriate. Additionally, the participants may not be part of any other psychological therapy or take any medication with psychoactive drugs until the study is completed. We further control for an unchanged physical activity level during the intervention.

A prior sample size calculation was performed using g*power 3 [47] based on (1) an expected medium effect size in the overall model according to cortisol and PTSD changes reported in previous studies [45], (2) the PTSD symptom severity, the trauma load and the number of potential stressors occurring during the intervention as covariates, and (3) the number of time points. The desired statistical power level was set at 0.95. The sample size calculation was corrected for an estimated dropout rate of 20%, according to other intervention studies that have already been performed in the Nakivale refugee settlement [48]. According to the power analysis, 159 participants are sufficient so that a total sample size of 198 participants is targeted to acknowledge potential dropouts.

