### Study design

The present project, which was also registered at www.drks.de before the start of data collection, contains two subsequent steps: (1) a PTSD screening in a large and representative sample of juvenile refugees from the DRC that will serve to identify participants eligible for inclusion in the intervention. A cross-sectional analysis comparing the physical activity levels of the refugees according to their PTSD symptom severity will serve to identify and balance potentially confounding variables. With regard to cross-sectional studies, it is difficult to make causal inferences because it is unknown if the parameter itself (e.g., being cardiovascularly fit) caused the benefit (e.g., reduced symptoms) or if other factors might have accounted for the resultant differences [49]. Therefore, (2) a longitudinal, prospective, and RCT will be implemented covering the ET intervention and two control conditions. *Group* (Exercise Training = ET, Alternative Intervention = AI, and Waiting-list Control = WC) serves as the between-subject factor. Eligible participants will be randomly assigned to one of the three conditions. The participants’ age, their traumatic load indicated by the number of experienced traumatic event types, the baseline PTSD symptom severity, and their physical activity level will serve as matching criteria across groups. The study utilizes a double-blind RCT design.

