#### Physical performance measures

In the *Shuttle Run Test* the participants have to run alternately between two lines that are 20 m separated from each other. The running speed will be given by intervals between tone signals. The interval between those signals will be reduced at every level. At the beginning of the test, the running speed is 8 km/h. Every minute it will increase by 0.5 km/h. One minute is roughly equivalent to one level of the shuttle run test. Every time the acoustic hint sounds, the participants have to reach the line. When a subject does not reach the line twice in a row, the test will be over for them. The graduated mileage will be noted and the appropriate VO_2max_ level can be read off [25].

The *International Physical Activity Questionnaire - Short Form* (IPAQ-SF; [60]) captures the general physical activity level of individuals by calculating the time of moderate and vigorous physical activity as well as the time that the participants spend walking and sitting. The questionnaire had also been used in an African context [61] and refers to the last 7 days.

The BMI will also be calculated by taking the body weight in kilograms and dividing it by the height [62].

The total body fat will be determined by using a skinfold caliper.

A detailed list of all measuring instruments and the times points at which they will be assessed is given in Fig. 2.

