#### Initial procedure

This study will purposively select 198 refugee adolescents using the quota sampling procedure that considers the proportions of different sexes. Hence, the sample will constitute 99 female and 99 male adolescent refugees each. Every third household in each selected zone will be selected as the target household until the desired number of participants is reached. Before the interview, content, procedure, risks, the right to withdraw, and confidentiality will be explained to each participant and written informed consent (signature or fingerprints in case of illiteracy) will be obtained. In addition to their parents, children, and adolescents will also be asked to give their informed consent. Potential participants as well as their legal authorized representatives will be fully informed about the study aims, the possible inconveniences of the clinical interview procedures, the compensation for participation, and the eligibility conditions of the treatment trial. After obtaining informed consent, participants will be screened regarding (1) their PTSD symptom severity, (2) potential exclusion criteria, in particular suicidality and psychotic symptoms according to the M.I.N.I., and (3) child protection issues according to their reports in the trauma event list and their clinical appearance during their contact with the care-takers and the interviewers. Participants with noticeable problems will receive a second check up by one of the PIs and will receive referrals if action is required. The screening will take about 60 min. Participants who are eligible for inclusion in the treatment trial will attend a more in-depth assessment that will take about 80 min. Afterwards, they will be randomly assigned to one of the three interventions.

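### The model adjusts the randomised comparison for traumatic events and stressors that arise after randomisation, which can remove part of the treatment effect or bias it

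*Protocol article*

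**What the plan says.** Under Statistical analysis, the main analysis is a "repeated-measure, mixed-model approach in order to identify significant changes in the main outcome variables between the three groups". The next statements bring in baseline PTSD severity and then add: "Potential confounding variables, such as the exposure to potentially traumatic events during the course of the intervention, will be used as covariates". No model restricted to baseline covariates is named as primary.

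Under Participants, the sample size is said to rest partly on three covariates: PTSD symptom severity, trauma load and "the number of potential stressors occurring during the intervention as covariates".

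On timing, Initial procedure describes the in-depth baseline assessment and continues: "Afterwards, they will be randomly assigned to one of the three interventions". Study design also places allocation after the t1 measures. Anything that happens during the 8-week programme is therefore post-randomisation.

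Study design lists variables to be balanced across groups at allocation: age, number of traumatic event types, "the baseline PTSD symptom severity, and their physical activity level will serve as matching criteria across groups".

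**The concern.** A confounder of a randomised comparison would have to influence which group a participant is in. An event that happens after allocation cannot do that, so the stated reason for adjusting does not apply. The reverse is possible: the assigned group may influence the covariate. WC adolescents receive no programme, while ET adolescents attend three supervised sessions a week. Adolescents whose symptoms improve may also meet, or report, fewer stressors.

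If either happens, adjustment does two things. It subtracts whatever part of the effect runs through exposure (mediation). It also compares participants with equal exposure but different allocation, who then differ in any unmeasured vulnerability that drives both exposure and symptoms (collider bias). The estimate would no longer be the effect of being assigned to ET, which is what the first hypothesis is about. Because the article itself fixes the choice, and in two places, it is not a detail left to an unseen analysis plan.

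**Working it through.** **1. The plan's own sample size.** The inputs from Participants are a medium effect, power 0.95 and 20% dropout. The assumed inputs are Cohen f = 0.25, alpha 0.05, m = 4 time points and correlation ρ = 0.5; the article gives no alpha or correlation. For the between-groups test in a repeated-measures ANOVA with three groups, the noncentrality is λ = f²·N·m / (1 + (m − 1)ρ). With N = 159:

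λ = 0.0625 × 159 × 4 / 2.5 = 15.9, on 2 and 156 degrees of freedom.

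The smallest N in multiples of three that reaches power 0.95 is 159, which matches the plan. The match is not unique (m = 2 with ρ = 0.25 also gives 159), but it uses no covariate term. As a cross-check, a one-way ANCOVA with 2 numerator degrees of freedom gives 251 with either 0 or 3 covariates, so the covariate count does not drive the figure. For dropout, 159 / 0.8 = 198.75, against 198 stated, a negligible difference.

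**2. What adjustment does to the estimate.** Let T be allocation (1 = ET, 0 = a comparator), M exposure during the intervention, Y the symptom score and U an unmeasured vulnerability. Disturbances are scaled to variance 1:

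- M = −a·T + u·U + √(1 − u²)·e₁
- Y = −d·T + b·M + u·U + √(1 − u²)·e₂

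The effect of assignment is −(d + a·b). Because E[U | T, M] = u(M + a·T), the coefficient of T after adjusting for M is −d + a·u². The shift is a·b (mediated part) plus a·u² (collider part). Both vanish if a = 0.

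**3. Numbers.** All path values are assumptions. The simulation used two arms of 53 (159 / 3), one post-treatment score, two-sided 5% tests and 4,000 runs per row. It is a simplification of the three-group mixed model.

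| d | a | b | u | Effect of assignment | Adjusted (formula) | Simulated: unadjusted / adjusted | Share lost | Rejection rate: unadjusted / adjusted |
|---|---|---|---|---|---|---|---|---|
| 0.5 | 0 | 0.3 | 0.5 | −0.50 | −0.50 | −0.499 / −0.498 | 0% | 0.64 / 0.74 |
| 0.5 | 0.2 | 0.3 | 0 | −0.56 | −0.50 | −0.560 / −0.499 | 0.06/0.56 = 11% | 0.79 / 0.72 |
| 0.5 | 0.5 | 0.3 | 0 | −0.65 | −0.50 | −0.644 / −0.495 | 0.15/0.65 = 23% | 0.88 / 0.68 |
| 0.5 | 0.2 | 0.3 | 0.5 | −0.56 | −0.45 | −0.559 / −0.450 | 0.11/0.56 = 20% | 0.73 / 0.66 |
| 0.5 | 0.5 | 0.3 | 0.5 | −0.65 | −0.375 | −0.651 / −0.378 | 0.275/0.65 = 42% | 0.85 / 0.48 |
| 0 | 0.2 | 0 | 0.5 | 0 | +0.05 | 0.002 / 0.053 | n/a | 0.053 / 0.062 |
| 0 | 0.5 | 0 | 0.5 | 0 | +0.125 | 0.002 / 0.126 | n/a | 0.050 / 0.100 |
| 0 | 0.5 | 0 | 0.7 | 0 | +0.245 | 0.005 / 0.247 | n/a | 0.053 / 0.281 |

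In the last three rows there is no treatment effect at all, so the rejections in the final column are type I errors. Here they point against ET. If allocation raised reported exposure instead (a negative), the collider term a·u² would change sign and favour ET.

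**The case against.** The strongest reply is that traumatic events in a refugee settlement may be largely external to the trial. If allocation leaves exposure and its reporting untouched, adjustment is unbiased and gains precision: the first row of the table shows −0.50 either way, with power rising from 0.64 to 0.74. This stands as a possibility. The documents offer no evidence for or against it, and a primary analysis should not depend on it when baseline covariates offer precision without the risk.

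A second reply concerns mechanism. Time in supervised sessions cannot separate ET from AI, because both attend three 45-minute sessions a week for 8 weeks. That is correct. This route matters only for comparisons with WC; between ET and AI only a route through symptom change or reporting is left.

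Two further readings are tempting but go beyond the text. A reader might infer that the model conditions on the treatment itself, because Participants says "We further control for an unchanged physical activity level during the intervention" and the IPAQ-SF "refers to the last 7 days", so 3 × 45 = 135 minutes a week of assigned sessions could register as a change. The sentence names no covariate, instrument or exclusion rule, and the Statistical analysis section does not mention activity. It can equally be read as a check on activity outside the programme. A reader might also infer selective loss of participants who deteriorate, from "Additionally, the participants may not be part of any other psychological therapy or take any medication with psychoactive drugs until the study is completed". The article does not say that anyone who later starts therapy or medication is removed from the analysis. Neither reading is part of this point.

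**Conclusion.** The point holds in conditional form. The plan states, in both the analysis and the sample size text, that the group comparison is adjusted for variables arising after randomisation, and it labels them confounders, which they cannot be. A reader might conclude that part of the effect is certainly adjusted away; the documents do not support that, since bias needs allocation to affect exposure or its reporting.

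The size depends entirely on assumed paths. The share lost runs from nothing, through about 11% to 23% by mediation alone, to about 42% when exposure falls by 0.5 SD and a common cause is present, with power falling from 0.85 to 0.48 in that case. With no true effect and the same 0.5 SD fall, type I error reaches about 0.10 to 0.28 for common-cause loadings of 0.5 to 0.7. With a 0.2 SD fall it stays near nominal (0.062). So the error rate is a serious matter only when the effect on exposure is strong, but the plan has no means of ruling that out in advance.

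**What to change.** In Statistical analysis, limit the primary mixed model to covariates measured at or before t1: baseline CAPS-CA-5, baseline trauma load, age, sex and baseline physical activity. Apart from sex, which is the quota variable in sampling, these are the listed matching criteria. Report exposure to traumatic events and stressors during the intervention in a table by arm, and keep the event-adjusted model as a labelled sensitivity analysis. In Participants, remove stressors during the intervention from the covariates listed for the sample size.

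The cost is a change to the covariate statements in these two sections, with no new data. If exposure is in fact unaffected by allocation, some precision is given up (0.64 against 0.74 in the illustration, which includes no baseline covariates); the baseline covariates should recover part of it. Since 159 is reproduced without a covariate term under the stated assumptions, 159 and 198 need not change. The Trial status section reports no recruitment yet, so at that stage the change could be made before any outcome data existed.

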#### Methods to protect against sources of bias

All participants who were not excluded through allocation will be randomized by a computer-generated program into the ET, AI, and WC groups. Furthermore, the interviewers do not know to which group the participants belong. All participants are asked to not talk about their intervention at any time point. The trainers are also blinded regarding the hypotheses of the researchers and the intervention under investigation. To acknowledge potential effects of allegiance, trainers are not informed about expected differences in the effectiveness of the interventions. Data analysts are blinded to group allocation. Blindness will be set aside when a participant is (1) suicidal, (2) acutely in danger, (3) overwhelmed by the intervention, (4) develops an additional psychological disorder, (5) loses a massive amount of weight, or (6) suffers under malnutrition. All names will be pseudonymized and anonymized and can only be undone by HB. Furthermore, 15% of the CAPS-CA-5 interviews are reassessed by a second interviewer to establish inter-rater reliability of the PTSD diagnosis and symptom severity.

#### Ethics approval and consent to participate

The Ethical Review Boards of the Medical School Hamburg approved the study. Additionally, further permission will be sought from the Uganda National Council for Science and Technology. Informed consent will be sought from each prospective participant and the participant’s legally authorized representative. If any participant is likely to be susceptible to undue influence or coercion, the investigators will enforce additional safeguards in the study to protect such participants. Additional referrals will be offered to patients suffering from acute suicidality or other issues that require acute treatment. As the provision of mental health services in the refugee settlement is sparse we shall refer patients with acute mental health problems to Mbarara Hospital Referral Department of Psychiatry for further treatment. Each participant of the ET, AI, and WC groups will receive 20,000 Uganda shillings, equivalent to US$7, for compensation of their time and participation. In case of a significantly positive treatment effect, additional ET will be offered to participants from the AI and WC groups after completion of the study to ensure access to a beneficial intervention. Potential study participants and their parents must provide written informed consent before they can be included in the study. Personal information about potential and enrolled participants will be collected and stored separately from other study data and will be only accessible for the assessors who contact the participants for data assessment. The study dataset does not include personal information and will be analyzed by the coordinating study site. In case of an unexpected serious adverse event (e.g., life-threatening event, permanent damage, or death) over the course of the study, the coordinating site will alert the PI who will report the serious adverse event to the local Ethics Committee. The Ethics Committee and the study team will then decide in accordance with the best interest of the patient if the study procedures are continued or terminated.

## Discussion

This study is designed to investigate the effects of an ET program on the cortisol levels and symptoms of young individuals with PTSD. There have been previous trials examining the relationship between exercise and PTSD, that have found significant improvements in symptom severity through ET [12–14]. In regard to the relationship between cortisol and PTSD, most studies confirmed lower cortisol levels in PTSD patients [39, 40, 63], even though in some cases higher cortisol levels were found [38]. The relationship between cortisol and exercise in healthy subjects, confirms changes through an implementation of an ET, but the response of cortisol varied in those studies and depended on age [18, 30, 31, 35], showing no different secretion due to the physical activity status for adolescent students [35]. The aim of the described study is a combination of three factors: ET, PTSD symptom severity, and cortisol/DHEA. There is only one related study investigating this subject, using a *Mindfulness-based Stretching* intervention in an adult sample. Those researchers found significant changes in cortisol levels and also an improvement in PTSD symptom severity after the participants completed the 8-week ET program. They confirmed that improved PTSD scores were associated with a normalization of cortisol levels [45]. It is unclear whether this intervention will be intense enough for inducing cortisol changes in the present younger population [25]. since a higher exercise intensity is needed to induce changes in cortisol levels after an ET program [26]. Taken together, PTSD patients have a dysfunction in the HPA-axis [37] and we expect the cortisol levels of PTSD patients to change by implementing an ET program. Furthermore, we assume that the change in cortisol levels will be associated with an improvement of the PTSD symptoms.

The present study introduces an interventional program that is easy to implement and, compared to most psychological interventions, has the advantage of being administered in groups. It is generally accepted that group interventions that can be administered by laymen are more cost-effective than therapeutic interventions in a one-to-one setting that require extensive psychotherapeutic expertise. However, besides face validity, the cost-effectiveness of an ET intervention as proposed in the present publication has not yet been evaluated in terms of direct and indirect costs. Thus, the present study provides further promising targets for interdisciplinary research on economic aspects of different potential health services in refugee settings.

Another advantage is that ET is not difficult to introduce and no additional costly materials are needed. This is in particular important for an ample provision of interventions in resource-poor settings. Another benefit of the present work lies in the recruitment of the participants in the refugee settlement in Uganda, Africa, who are highly affected by PTSD [64]. Previous research that strictly used cross-sectional study designs offers a limited explanation for the aim of the present work. Therefore, in addition to a cross-sectional program, a longitudinal study design was planned. This might provide the research field with more meaningful and confirmatory results. In sum, there is no study regarding the effect of an ET program on cortisol levels and symptom severity in adolescent individuals with PTSD. Therefore, the presented longitudinal RCT will close this gap and will allow for a new promising approach to overcome trauma-related suffering in PTSD-affected refugee populations.

### Trial status

TRLS-D-18-00245R, 18 June 2018, no recruitment yet.

## Abbreviations

ACTH: Adrenocorticotropic hormone
AI: Alternative Intervention
BMI: Body Mass Index
CAPS-CA-5: Clinical Administered PTSD Scale for DSM-5 Child/Adolescent Version
CAR: Cortisol awakening response
CRH: Corticotropin-releasing hormone
DHEA: Dehydroepiandrosterone
DHEAS: Dehydroepiandrosterone sulfate
DSM: Diagnostic and Statistical Manual of Mental Disorders
ET: Exercise training
HPA-axis: Hypothalamic-pituitary-adrenal axis
HR_max_: Maximal heart rate
IPAQ-SF: International Physical Activity Questionnaire - Short Form
M.I.N.I: Mini International Neuropsychiatric Interview
PHQ-A: Patient Health Questionnaire
PTSD: Post-traumatic stress disorder
RCT: Randomized controlled trial
SDQ: Strengths and Difficulties Questionnaire
UCLA: Child/Adolescent PTSD Reaction Index for DSM-5
UNHCR: United Nations High Commissioner for Refugees
VO_2_: Volume of oxygen
VO_2max_: Maximum rate of oxygen consumption
WC: Waiting-list control
